### **8.3 Safety assessment of laboratory and other inspections**

Laboratory examination indicators include hematology, blood biochemistry, urine routine examination, histopathology, serum virology examination and bone marrow

biopsy, all of which must be carried out in a laboratory accredited by the hospital. The normal range of all laboratory test items, as well as the updates during the research period, should be recorded on the corresponding page of CRF.

#### **8.4 Suitability of measurement**

All effectiveness and safety assessments used in this study are standard assessments, which are widely used and recognized as reliable, accurate and relevant assessments.

### **9 Data management**

In this study, patient data will be recorded into the designated CRF and sent to the data system confirmed by the researcher for integration with data from other sources.

The staff of the research center shall be responsible for filling in the CRF. For all patients who have signed the ICF and screened qualified to participate in the study, the investigator or authorized staff must carefully record the items in the CRF and ensure no blank or missing items (unrecorded blanks should be filled in according to the actual situation). All data in the CRF must be checked with the original data of the patient to ensure that it is correct.

The investigator must paste the original or copy laboratory sheets on the patient's research medical record. For abnormal laboratory or examination data, the investigator must verify and clarify whether it has clinical significance. The investigator should strictly follow the CRF instructions to fill in the form.

### **10 Statistics and statistical analysis**

All statistical analysis will be performed with SPSS (18.0 or higher version) software. In this study, the variables obtained at each observation time were statistically described, unless the plan clarifies no need for statistical description at a particular time point. The *P* value less than or equal to 0.05 is judged as a criterion for statistically

significance. The description of quantitative indicators will calculate the mean, standard deviation, median, minimum and maximum. The description of classification indicators includes the number of cases and percentages of various types. Categorical variables will be statistically described using the frequency and percentage of each category. The final analysis of the study will be based on the data collected throughout the entire study.

## 10.1 Calculation of sample size

### Critical clinical data:

#### 1. Efficiency of anti-PD-1 antibody

Currently, three literatures were published reporting anti-PD-1 antibody to treat relapsed and refractory NKT cell lymphoma, with a total of 15 patients. The curative effects of the three articles are as follows:

##### Short-term efficiency:

|                  | N  | ORR      | CR       | PR       |
|------------------|----|----------|----------|----------|
| Hong Kong, China | 7  | 100%(7)  | 28.6%(2) | 71.4%(5) |
| Henan, China     | 7  | 57.2%(4) | 28.6%(2) | 28.6%(2) |
| Nanchang, China  | 1  | 100%(1)  | 100%(1)  |          |
| Summary          | 15 | 80%(12)  | 33.3%(5) | 46.7%(7) |

**Long-term survival:** no report.

#### 2. Efficiency of Chidamide

##### Short-term efficiency

|                         | N  | ORR     | CR     | PR     |
|-------------------------|----|---------|--------|--------|
| Refractory and Relapsed | 20 | 60%(12) | 30%(6) | 30%(6) |

**Long-term survival:** Median PFS = 7.0 (months)

Therefore, if ORR (Objective Effective Rate) is used as the primary outcome measures, the sample size is as follows:

- The phase Ib study used a “3+3” dose escalation scheme to determine the

maximum tolerated dose (MDT) of chidamide. There are three dose groups (20mg, 25mg, 30mg) for chidamide, with 3 to 6 patients in each dose group.

**Approximately 9 to 18 patients are needed for stage Ib.**

- The phase II study adopts the Simon two-stage optimal design method. The main purpose of the research is to use the maximum tolerated dose determined in phase Ib as the recommended dose to preliminarily evaluate the ORR of treatment of chidamide combined with anti-PD-1 antibody in the treatment of refractory and relapsed Extranodal NK/T-cell lymphoma. According to previous studies,  $P_1$  is supposed as 0.8 (expected effective rate) and  $P_0$  as 0.55 (poor effective rate), with  $\alpha=0.05$  and  $\beta=0.8$ . The best two-stage design is (4/7, 19/28). That is, 7 patients were enrolled in the first stage, and if only 4 or fewer patients were effective, the trial was terminated. Otherwise, the trial enters the second phase and 21 more patients will be enrolled. That is, a total of 28 patients will be enrolled in the phase II study. A total of 37 to 46 patients will be enrolled in stage Ib and II. The study loss rate was set at 10% and a total of 40-50 patients will be enrolled. If the number of effective cases in all patients in the two stages exceeds 19, there is an 80% probability that the test drug is effective.

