| Rationale                  | 
Extranodal natural killer/T cell lymphoma (ENKTL) is a distinct lymphoid neoplasm with aggressive course and poor outcomes. Optimal treatment strategies for relapsed or refractory disease are controversial. In small retrospective studies have observed promising response and survival rates in patients treated with L-asparaginase. In several prospective study that examined relapsed/refractory (RR) patients treated with SMILE outside a trial setting, the efficacy sounds good. But treatment related mortality was 7%. The regimen has toxicity, with careful attention to adverse effects and skill acquired through experience. Therefore, the development of novel effective therapies or strategies for this population is urgently. ENKTL are invariably infected by Epstein-Barr virus (EBV). EBV-infected lymphoma cells upregulate programmed death ligand 1 (PDL1), ligand of the inhibitory receptor programmed death 1 (PD1) on T cells. Ligation of PDL1 on lymphoma cells with PD1 on effector T cells suppresses T-cell cytotoxicity. The PDL1/PD1 axis is therefore a potential mechanism for ENKTL to avert effector T-cell targeting. PD1 blockade with pembrolizumab was a potent strategy for ENKTL failing L-asparaginase regimens in several reports. However, the complete remission (CR) rate reaches 30% merely and the remission time is short. Therefore, it is necessary to explore new combinatorial therapeutics with immunotherapy in RR-ENKTL. Chidamide, an oral subtype-selective histone deacetylase inhibitor (HDACi) monotherapy was effective on the patients with RR-ENKTL in our study. Objective response rate (ORR) was 50.0% (6/12) with CR rate 33.3% (4/12). All four CR patients were still in disease-free more than 6.9 months (6.9-10.5). Recent studies on the role of epigenetics in immune evasion have exposed a key role for epigenetic modulators in augmenting the tumor microenvironment and restoring immune recognition and immunogenicity. Theoretically, anti-PD-1 antibody combination with epigenetics agents can improve the curative effect. Thus, we carried out a single, open-label, multicenter clinical trial enrolled patients with RR-ENKTL to safety and efficacy of sintilimab in combination with chidamide.
 |

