| Sample Size:                             | Approximately 37-40 patients.                                                                                                                                                                                                                                                                                                                                                                                                                                                                                                                                                                                                                                                                                                                                                                                                                               |
| Statistical analysis                     | 
Study Hypotheses:
 
 
• ORR based on investigators for patients treated with sintilimab plus chidamide to be 80% with a one-sided type 1 error rate of 5% and at least 80% power.
 
• Simon's two-stage design was used.
 
• Sample size for phase II of the study was calculated assuming the target ORR of combination treatment to be 80% with a one-sided type 1 error
 
                                                                                                                                                                                                                                                                                                                                                                                                        |

|  |                                                                                                                                                                                                                                                                                                                                                                                         |

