of PD-L1, and potential mechanism is via EBV triggering of latent membrane protein 1 (LMP1), which then upregulates PD-L1 expression through activation of the mitogen-activated protein kinases pathway/nuclear factor kappa B pathway. PD-1/PD-L1 show promising monotherapy efficacy and well tolerance in ENKTL failing to asparaginase-based treatment in current early-phase trials and retrospective studies. The ORR was about 38%-68% and CR rate was about 24%-36%. However, the median progression-free survival (PFS) and duration of response (DOR) are relatively short. Combining other therapies might be an approach to improve the efficacy.

Histone deacetylase inhibitors (HDACi) have shown promising effect in peripheral T cell lymphoma (PTCL). Chidamide an oral subtype-selective histone deacetylase inhibitor (HDACi) has been approved by National Medical Products Administration (NMPA) for the treatment of refractory or relapsed PTCL. In phase I study of chidamide monotherapy in patients with advanced solid tumors and lymphomas. Patients received oral doses of 5, 10, 17.5, 25, 32.5, or 50 mg chidamide either twice (BIW) or three times (TIW) per week for 4 consecutive weeks every 6 weeks. Two incidences of grade 3 diarrhea, nausea and vomiting of first-cycle dose-limiting toxicity (DLT) were observed in the first two patients enrolled in the 50 mg TIW cohort. Thus, gastrointestinal side effects were determined to be DLTs in the 50 mg TIW cohort. No DLTs were observed in other cohorts for both BIW and TIW regimens. In an exploratory phase II trial, 19 patients with relapsed or refractory PTCL were randomized to receive 30 or 50 mg twice per week for 2 weeks, followed by 1 week of rest. The ORR was 11.1% for the 30 mg and 40.0% for the 50 mg. One patient in the 50 mg arm experienced drug-related grade 4 thrombocytopenia. Based on the overall results from the phase I and exploratory phase II trials, patients in the pivotal phase II study were orally administered with chidamide of 30mg. However, efficacy

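### P0 = 0.55 is below both single-agent response rates tabulated in section 10.1 and P1 = 0.80 equals one of them, so meeting the 20/28 rule does not by itself show that the combination adds to either drug

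*Protocol*

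**What the plan says.** Section 10.1 opens with historical response rates. Three reports of anti-PD-1 antibody pool to an ORR of 80% (12/15), and chidamide has 60% (12/20). Citing previous studies, it then takes a target that "is supposed as 0.8 (expected effective rate") and a null "as 0.55 (poor effective rate"), with no step leading from the tables to either value. The synopsis states the error rates: target ORR "to be 80% with a one-sided type 1 error rate of 5% and at least 80% power". Section 10.1 continues: "The best two-stage design is (4/7, 19/28"), and "if only 4 or fewer patients were effective, the trial was terminated". More than 19 responders among 28 counts as success, which the section describes as an 80% probability that the drug is effective.

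Elsewhere the single-agent figures are lower. For PD-1/PD-L1 monotherapy, section 1.1 reports: "The ORR was about 38%-68% and CR rate was about 24%-36"%. For chidamide alone, the synopsis and section 1.1 report: "Objective response rate (ORR) was 50.0% (6/12) with CR rate 33.3% (4/12"). After noting that PFS and duration of response are short on monotherapy, section 1.1 adds: "Combining other therapies might be an approach to improve the efficacy".

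**The concern.** In a single-arm trial the null rate is the only comparator, so it fixes what a positive result means. On the data printed in 10.1, the rate labelled poor is worse than either drug given alone, and the rate labelled expected is no gain over anti-PD-1. The smallest successful result, 20/28 = 71.4%, is below the 80% that the section attributes to anti-PD-1 alone.

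The 5% error rate protects against a true ORR of 55% or less. It does not protect against a combination that performs no better than one of its components. Because the trial is motivated by improving on monotherapy, a positive result could be taken as support for combining the drugs when the rule has not tested that. The protocol also gives two sets of single-agent rates and does not say which one supports 0.55, so the main design input cannot be traced.

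**Working it through.** **Inputs.** From section 10.1: P0 = 0.55, P1 = 0.80; stop after stage 1 with 4 or fewer responders of 7; success with at least 20 of 28. From the synopsis: one-sided 5%, power at least 80% (10.1 prints β = 0.8, which makes sense only as power). Single-agent rates: 60% and 80% (10.1); 50% and 38% to 68% (section 1.1).

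**Formula.** P(success | p) = Σ over x = 5, 6, 7 of P(X₁ = x; 7, p) × P(X₂ ≥ 20 − x; 21, p).

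**The plan's own figure first.**
- p = 0.55: 0.2140 × 0.0964 + 0.0872 × 0.1971 + 0.0152 × 0.3413 = 0.043.
- p = 0.80: 0.2753 × 0.8915 + 0.3670 × 0.9569 + 0.2097 × 0.9856 = 0.803.

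Both meet the stated error rates. A full search over two-stage designs returns 4/7, 19/28 as the Simon optimal design for these inputs (expected sample size under P0 13.6). The arithmetic is right.

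**The same rule at the protocol's single-agent rates.**

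| True ORR | What the rate represents | P(success) |
|---|---|---|
| 38% | bottom of the PD-1/PD-L1 range, 1.1 | 0.02% |
| 50% | chidamide, 1.1 and synopsis | 1.3% |
| 53% | midpoint of 38% to 68% | 2.8% |
| 55% | P0 | 4.3% |
| 60% | chidamide, 10.1 | 11.3% |
| 68% | top of the PD-1/PD-L1 range, 1.1 | 34.5% |
| 80% | anti-PD-1, 10.1, and also P1 | 80.3% |

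**Precision of the historical rates** (exact 95% intervals): 12/15, 51.9% to 95.7%; 12/20, 36.1% to 80.9%; 6/12, 21.1% to 78.9%.

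**What the planned interval can exclude.** The synopsis and section 10.4 plan a 95% exact interval (two-sided; Clopper-Pearson). Its lower limit L solves P(X ≥ x; 28, L) = 0.025.

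| Responders of 28 | Observed | Lower limit |
|---|---|---|
| 20 | 71.4% | 51.3% |
| 21 | 75.0% | 55.1% |
| 22 | 78.6% | 59.0% |
| 23 | 82.1% | 63.1% |
| 24 | 85.7% | 67.3% |
| 25 | 89.3% | 71.8% |
| 26 | 92.9% | 76.5% |
| 27 | 96.4% | 81.7% |

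Excluding 60% takes 23/28, excluding 68% takes 25/28, and excluding 80% takes 27/28. With the stage 1 stop in place and a true ORR of 80%, these are reached with probability 47.8%, 15.9% and 1.5% (the formula above with 20 replaced by 23, 25 and 27).

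At exactly 20/28 the two-stage test succeeds at one-sided 5% while the planned two-sided interval still contains 55%. The report should explain this, because both will be shown.

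**The case against.** The strongest reply is that the protocol plans no superiority claim over sintilimab or chidamide. Section 10.1 describes phase II as a preliminary evaluation of ORR, and the primary objective is the efficacy of the combination. The gap that section 1.1 and the synopsis rationale name is mainly low CR and short remission, not ORR. That no single-arm trial can isolate a component's contribution is a general limit.

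The historical rates are also weak. The 80% pools 15 patients, with the two series of 7 giving 57% and 100%. A null need not sit at the top of a historical range. Against section 1.1, 0.55 is above chidamide's 50% and above the midpoint of 38% to 68%, where the rule passes only 1.3% and 2.8% of the time. The two sets may not even describe the same thing: section 1.1 includes PD-L1 antibodies and cites other reports, and the chidamide counts may be different data cuts. Patients previously treated with either drug class are now eligible, so none of these rates may fit the enrolled population exactly.

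Most of this stands, and it bars three stronger readings that a reader might infer:

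- *A positive phase II cannot show any added effect.* This is true of merely meeting the success rule. It is not true of an extreme result: 27/28 would exclude even 80%, although as a comparison with a historical figure only.
- *The two sets of rates contradict each other.* They differ and are not reconciled. The documents do not establish that they measure the same quantity.
- *0.55 is wrong.* It can be defended on the section 1.1 figures.

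The reply does not answer the narrower point. Section 10.1 presents 0.55 as following from previous studies, and the only studies it lists give higher rates.

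**Conclusion.** The concern holds in limited form. P0 and P1 are not supported by the data that 10.1 sets out for them: P0 is 5 points below the tabulated chidamide rate and 25 points below the tabulated anti-PD-1 rate, and P1 equals the latter. A combination with a true ORR of 60% would pass 11.3% of the time, over twice the nominal 5%. At 68% it would pass 34.5% of the time, and at 80%, 80.3%. On the lower figures in section 1.1 the problem largely disappears. The size therefore depends on which historical set is accepted, and the protocol does not say.

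The probabilities use the stage 1 rule of 10.1. The synopsis words that rule as stopping below 4 of 7, which would raise success to 5.4%, 14.0%, 41.7% and 89.2% at 55%, 60%, 68% and 80%. They also treat each historical rate as known, which small series do not justify. The design calculation itself is sound. This is a should-fix point about the basis of P0 and the claim attached to a positive result.

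**What to change.** Keep P0, P1, 28 patients and the boundaries.

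1. Reconcile the single-agent rates in sections 1.1 and 10.1, saying why they differ. State which set 0.55 rests on, and note the imprecision of the small series.
2. Replace the closing sentence of 10.1, which turns more than 19 responders into an 80% probability of effectiveness. The 80% is power at a true ORR of 80%, not the probability that the drug works. Say instead that more than 19/28 shows only that ORR exceeds 55% at one-sided 5% under the two-stage rule, and that no claim of benefit over sintilimab or chidamide alone rests on it.
3. If reporting benchmarks are wanted, tie them to the planned two-sided 95% Clopper-Pearson interval: at least 23/28 to exclude 60%, 25/28 to exclude 68% and 27/28 to exclude 80%. State that at a true ORR of 80% these are reached with probability about 48%, 16% and 2%. Thresholds of 22/28 and 24/28 would pass a one-sided 5% test but sit beside intervals that still contain 60% and 68% (lower limits 59.0% and 67.3%).

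The cost is protocol wording only, with no extra patients. The downside is that a result of 20 to 22 of 28 will support a weaker claim than the current text suggests.

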**DOCUMENT HISTORY**

| Document          | Date of Issue | Overall Rationale                                                                                                    |
|--------------------------|----------------------|-----------------------------------------------------------------------------------------------------------------------------|
| Amendment 02      | 08-August-2019       | Modifying the inclusion criteria, patients who were previously treated with PD-1/L1 antibodies or chidamide were permitted. |
| Amendment 01      | 20-January-2019      | Modifying several of the inclusion criteria to better define the appropriate participant population.                        |
| Original Protocol | 14-July-2018         | Not applicable                                                                                                              |

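### Section 10.1 presents 80% power as the probability that the drug is effective, and a pass rejects an ORR of 55% without by itself showing gain over either single agent

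*Protocol*

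**What the plan says.** Protocol Section 10.1 builds phase II on a Simon optimal two-stage design, with rates said to come from previous studies. The target P1 "is supposed as 0.8 (expected effective rate") and the null P0 "as 0.55 (poor effective rate"). Alpha is 0.05 and beta is printed as 0.8. The result reads "The best two-stage design is (4/7, 19/28"). At stage 1, "if only 4 or fewer patients were effective, the trial was terminated". The section closes by interpreting a positive result: if responders over both stages number more than 19, that is, the count "exceeds 19, there is an 80% probability that the test drug is effective".

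The Synopsis describes the same design differently, "with a one-sided type 1 error rate of 5% and at least 80% power". Its Study Design row also stops stage 1 at fewer than 4 responders of 7, where Section 10.1 stops at 4 or fewer.

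Single-agent rates appear in two places:

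- **Section 10.1 tables:** anti-PD-1 12/15 = 80%; chidamide 12/20 = 60%.
- **Section 1.1:** for PD-1/PD-L1 agents, "The ORR was about 38%-68% and CR rate was about 24%-36"%; for chidamide 6/12 = 50%.

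Under Amendment 02, "patients who were previously treated with PD-1/L1 antibodies or chidamide were permitted". Its summary of changes lists no change to Section 10.1.

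**The concern.** The closing sentence of Section 10.1 is the only place where the protocol says what a pass means, and it reverses a conditional probability. Power is the chance of passing given an effective drug. The sentence reports it as the chance of an effective drug given a pass. The Synopsis calls the same 80% power, so the document disagrees with itself, and the wrong version could carry into the report.

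The second issue is what a pass can be compared with. The Synopsis rationale is that adding chidamide should improve on PD-1 blockade. Yet the null rate is lower than both single-agent rates tabulated just before it, and the target only equals the anti-PD-1 rate there. The Section 1.1 rates are lower. The protocol does not say which rates 55% is meant to represent, so a reader cannot tell what rejecting 55% establishes about the combination.

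**Working it through.** **Inputs.** From Section 10.1: p0 = 0.55, p1 = 0.80, continue if more than 4 of 7 respond, pass if more than 19 of 28 respond. From the Synopsis: one-sided alpha 5%, power at least 80%.

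**1. Reproducing the design.** The chance of passing at true rate p is

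P(pass | p) = sum over x = 5, 6, 7 of P(X1 = x) × P(X2 ≥ 20 − x), with X1 ~ Bin(7, p) and X2 ~ Bin(21, p).

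| x | P(X1 = x), p = 0.80 | P(X2 ≥ 20 − x) | product | P(X1 = x), p = 0.55 | P(X2 ≥ 20 − x) | product |
|---|---|---|---|---|---|---|
| 5 | 0.2753 | 0.8915 | 0.2454 | 0.2140 | 0.0964 | 0.0206 |
| 6 | 0.3670 | 0.9569 | 0.3512 | 0.0872 | 0.1971 | 0.0172 |
| 7 | 0.2097 | 0.9856 | 0.2067 | 0.0152 | 0.3413 | 0.0052 |
| Sum | | | **0.8033** | | | **0.0430** |

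Power is 0.803 and one-sided type I error 0.043. A full search with p0 = 0.55, p1 = 0.80, alpha ≤ 0.05 and beta = 0.2 returns 4/7, 19/28 as the optimal design. The design is right; the printed beta of 0.8 is the power.

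**2. What the sentence claims.** The probability that the drug is effective given a pass needs a prior. In a two-point illustration (true ORR either 55% or 80%) with assumed prior π on 80%:

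P(80% | pass) = π × 0.8033 / [π × 0.8033 + (1 − π) × 0.0430].

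- π = 0.1: 0.0803 / (0.0803 + 0.0387) = 67%
- π = 0.2: 0.1607 / (0.1607 + 0.0344) = 82%
- π = 0.5: 0.4017 / (0.4017 + 0.0215) = 95%

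The answer can lie on either side of 80%, so no fixed 80% follows from the design. The priors are assumptions, used only to show this.

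**3. Chance of passing at the protocol's own single-agent rates** (formula of step 1):

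| True ORR | Where the rate appears | P(pass) |
|---|---|---|
| 50% | Section 1.1, chidamide | 1.3% |
| 55% | p0 | 4.3% |
| 60% | Section 10.1, chidamide | 11.3% |
| 68% | Section 1.1, top of PD-1/PD-L1 range | 34.5% |
| 80% | Section 10.1, anti-PD-1; also p1 | 80.3% |

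**4. The stage-1 condition matters.** Section 10.1's figures hold only for stopping at 4 or fewer of 7. Under the Synopsis rule, x = 4 also continues, which adds 0.2918 × 0.0389 = 0.0114 at 55% and 0.1147 × 0.7693 = 0.0882 at 80%. Type I error becomes 0.0430 + 0.0114 = 0.054, above the nominal 5%, and power 0.8033 + 0.0882 = 0.892. With no stage-1 condition, 20 or more of 28 has error 0.058 and power 0.910.

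**5. Sensitivity to p0.** With p0 = 0.60 and p1, alpha and power unchanged, the optimal design is 7/11, 30/43: 43 patients rather than 28.

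**The case against.** The best defence is that the error is one misworded sentence and one misprint. The Synopsis states power correctly, and the thresholds, sample size and operating characteristics of Section 10.1 are exact. This stands: nothing in the design has to be recalculated.

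A reader might go further and infer that p0 and p1 both sit at or below the single-agent rates, so that success could never show benefit from the combination. The protocol does not support that. The target of 80% exceeds every single-agent summary rate given except the pooled 12/15. The null of 55% is above the 50% for chidamide in Section 1.1 and inside the 38% to 68% range for PD-1/PD-L1 agents. The 80% rate pools series of 7, 7 and 1 patients (exact 95% confidence interval for 12/15: 52% to 96%), and 12/20 is also imprecise (36% to 81%). Against 50%, the rule passes falsely only 1.3% of the time. Nor is a pass mark of 20/28 = 71%, below 80%, a defect: here the critical value lies between p0 and p1, as expected of a test powered at p1.

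A reader might also infer that the sponsor would present a pass as proof of superiority. Section 10.1 claims only a preliminary evaluation of ORR. The stated shortfall of PD-1 blockade is also largely in complete response rate and durability, which are separate outcomes here.

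What remains is that the interpretive sentence is false as written, and that the protocol gives conflicting reference rates without saying why 55% was chosen.

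**Conclusion.** The point holds in this limited form. The 80% in the closing sentence of Section 10.1 is P(pass both stages | true ORR 80%) = 0.803. It is not a probability that the drug is effective, and beta = 0.8 is the same confusion of power with its complement. A pass rejects an ORR of 55% or less at an exact one-sided level of 0.043. It does not by itself show gain over chidamide or anti-PD-1 alone: depending on which of the protocol's single-agent rates is the reference, a combination that adds nothing to it passes with probability from 1.3% (at 50%) to 80.3% (at 80%). These figures assume the Section 10.1 stage-1 rule and independent responses with a common rate.

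The amendment record shows no revisiting of p0 and p1 when Amendment 02 admitted patients pretreated with PD-1/L1 antibodies or chidamide. One might infer a specific loss of power from this. The protocol gives neither the expected share of such patients nor their response rate, so no figure can be supported.

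**What to change.** In Section 10.1:

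1. Replace the closing sentence with: *Continuing past stage 1 with more than 4 of 7 responses and then observing 20 or more of 28 rejects an ORR of 55% or less (exact one-sided type I error 0.043); the probability of this is 80.3% if the true ORR is 80%.*
2. Print beta as 0.2.
3. State that phase II tests ORR against 55% and does not test superiority over either single agent.
4. Justify 55% against the conflicting rates in Sections 10.1 and 1.1.
5. Reconcile the Synopsis stage-1 rule with Section 10.1. If the Synopsis rule were kept, the figures in item 1 would have to be 0.054 and 89.2%.
6. Note that p0 and p1 were not revisited when Amendment 02 opened the trial to pretreated patients.

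The cost is wording only: no added patients, visits or procedures while p0 stays at 55%. The downside for the sponsor is that the stated conclusion of a positive result becomes less favourable.

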|--|-----------------------------------------------------------------------------------------------------------------------------------------------------------------------------------------------------------------------------------------------------------------------------------------------------------------------------------------------------------------------------------------|
|  | 
rate of 5% and at least 80% power.
 

• ORRs were reported with two-sided 95% exact confidence intervals (CIs), and the number and percentage of patients in each response category were descriptively tabulated. DOR, PFS, RFS, and OS will be analyzed by Kaplan-Meier approach. Safety analyses will be presented descriptively.

 |
|--|-----------------------------------------------------------------------------------------------------------------------------------------------------------------------------------------------------------------------------------------------------------------------------------------------------------------------------------------------------------------------------------------|

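### Section 10.1 labels the 80% power as beta = 0.8 and then misreads it as an 80% probability that the drug is effective; the design itself is unaffected

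*Protocol*

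**What the plan says.** Section 10.1 describes the phase II design: "The phase II study adopts the Simon two-stage optimal design method". The target response rate "is supposed as 0.8 (expected effective rate") and the uninteresting rate is set "as 0.55 (poor effective rate"). Alpha is printed as 0.05 and beta as 0.8. The resulting design is given as "The best two-stage design is (4/7, 19/28"). At stage 1, "if only 4 or fewer patients were effective, the trial was terminated"; otherwise 21 more patients are enrolled, making 28. The section ends by saying that if the number of responders over both stages exceeds 19, "there is an 80% probability that the test drug is effective".

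The synopsis (Statistical analysis) gives the error rates differently. It assumes an ORR "to be 80% with a one-sided type 1 error rate of 5% and at least 80% power", and so treats the 80% as power. The synopsis (Study Design) also gives a stage 1 rule, under which the study stops only if the response is below 4 of 7.

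**The concern.** Two statements in section 10.1 are wrong as written.

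1. **Beta.** Beta is the type II error rate, so beta = 0.8 means 20% power. That contradicts the synopsis, and it cannot be the value from which the printed design was derived.
2. **The closing sentence.** Power is a probability about the data given an assumed true rate: P(more than 19 of 28 respond | ORR = 80%). The sentence turns it round into P(drug effective | more than 19 of 28 respond). The second quantity depends on how plausible efficacy was beforehand, and the protocol specifies no prior.

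The second error matters more. Correcting beta does not repair it, and this sentence is the only place where the protocol attaches a meaning to crossing the final boundary. Nowhere does the protocol say that 20 or more responders reject an ORR of 55% at one-sided 5%.

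**Working it through.** **Inputs.** From section 10.1: P0 = 0.55, P1 = 0.80, n1 = 7, stop if 4 or fewer respond, N = 28, success if more than 19 (that is, 20 or more) respond. From the synopsis: one-sided type I error 5%, power at least 80%.

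**Step 1. Reproduce the design.** The probability of declaring success at a true rate p is the sum over x = 5, 6, 7 of P(X1 = x) × P(X2 ≥ 20 − x), with X1 ~ Bin(7, p) and X2 ~ Bin(21, p).

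| x in stage 1 | Needed of 21 | p = 0.55 | p = 0.80 |
|---|---|---|---|
| 5 | 15 | 0.2140 × 0.0964 = 0.0206 | 0.2753 × 0.8915 = 0.2454 |
| 6 | 14 | 0.0872 × 0.1971 = 0.0172 | 0.3670 × 0.9570 = 0.3512 |
| 7 | 13 | 0.0152 × 0.3413 = 0.0052 | 0.2097 × 0.9856 = 0.2067 |
| Total | | **0.0430** (alpha) | **0.8033** (power) |

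So beta is 1 − 0.8033 = 0.197. An exhaustive search of two-stage designs up to N = 36 with alpha ≤ 0.05 and power ≥ 0.80 returns 4/7, 19/28 as the optimal design (expected N under P0 of 13.6). The plan's figure reproduces with beta = 0.2.

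**Step 2. Take beta = 0.8 literally.** Searching designs up to N = 19 with alpha ≤ 0.05 and power ≥ 0.20 gives 1/2, 5/6 (alpha 0.028, power 0.262). This is nothing like the printed design, so the printed 0.8 is the power under the wrong label.

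**Step 3. What the closing sentence would need.** Suppose only two rates are possible, 80% (effective) and 55% (not), with prior probability π of the first. The two-point form and every value of π are assumptions; the protocol has none. Then

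P(effective | success) = 0.8033π / [0.8033π + 0.0430(1 − π)].

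| π (assumed) | P(effective given success) |
|---|---|
| 0.05 | 0.0402 / (0.0402 + 0.0409) = 0.50 |
| 0.10 | 0.0803 / (0.0803 + 0.0387) = 0.67 |
| 0.30 | 0.2410 / (0.2410 + 0.0301) = 0.89 |
| 0.50 | 0.4016 / (0.4016 + 0.0215) = 0.95 |

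The value is 80% only at π of about 0.176. With a flat prior on the ORR (also an assumption), P(ORR > 55% | success) is about 0.99. The 80% is not a property of the design.

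**Step 4. Dependence on the stage 1 rule.** Under the synopsis rule, 4 of 7 continues. With the final boundary unchanged this adds the x = 4 term, which needs 16 of 21:

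- p = 0.55: 0.2918 × 0.0389 = 0.0114, so alpha = 0.0430 + 0.0114 = 0.0544.
- p = 0.80: 0.1147 × 0.7693 = 0.0882, so power = 0.8033 + 0.0882 = 0.8915.

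Alpha then exceeds 5%. The figures in Step 1 hold only under the section 10.1 rule.

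**The case against.** The strongest reply is that these are wording faults with no operational effect. The synopsis states the power correctly, and the printed boundaries can only be those of the 80% power design, so a statistician would recognise the slip in beta. Sample size, boundaries and error rates do not move. This stands, and it limits the weight of the point.

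A reader might infer more: that the trial report would attach an 80% probability of effectiveness to any success. The protocol does not support that. The synopsis plans ORR with two-sided exact 95% intervals and tabulated response categories. Section 10.2 (Primary outcome measures) summarises proportions with 95% intervals, and section 10.4 calls for a Clopper-Pearson interval. None of them asks for a probability that the drug works. The sentence is a faulty gloss in the sample-size section, not a planned analysis.

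A reader might also take the table of priors as showing that the sentence exaggerates the evidence. It does not. Above a prior of about 18% the printed 80% is too low; below it, too high. The table shows only that the figure cannot be derived.

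What the reply does not remove is that the closing sentence is false even with beta corrected, and that no correct statement of the final decision rule appears elsewhere in the protocol.

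**Conclusion.** The point holds as an error of labelling and interpretation. Beta should read 0.2, and the 80% is the power at a true ORR of 80%, not a probability of effectiveness. N = 28, the 4/7 and 19/28 boundaries and the exact-interval reporting are unchanged. The literal contradiction is 20% against at least 80% power. The misread 80% has no fixed correct value to replace it; the 50% to 95% range is illustrative and rests on assumed priors.

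The exact alpha of 0.043 and power of 0.803 rest on the section 10.1 rule of stopping at 4 or fewer of 7. They cannot be quoted for the whole protocol while the synopsis gives a different rule. The correction is worth making because it is cheap and because this sentence is the only stated meaning of the final boundary.

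**What to change.** In section 10.1:

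1. Replace beta = 0.8 with beta = 0.2 (power 80%).
2. Replace the last sentence with: *If 20 or more of 28 patients respond, having passed stage 1 with at least 5 of 7, H0: ORR ≤ 55% is rejected at one-sided 5% (exact alpha 0.043); the probability of this is 80% (exact 0.803) if the true ORR is 80%.*
3. Add that these figures assume stopping at 4 or fewer responders of 7.

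In the synopsis (Study Design), reconcile the stage 1 rule with section 10.1, since stopping only below 4 of 7 with the same final boundary gives alpha 0.054.

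The cost is a few lines of text. Patient numbers, the section 10.1 boundaries and the planned analyses do not change.
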